#### **9.4.3 Reporting of SAEs and AEs to FDA**

Any AE meeting the specified SAE criteria and being rated as related (possible, probable, definite) to fluoride varnish administration will be submitted to the FDA using the MedWatch voluntary reporting system (<https://www.accessdata.fda.gov/scripts/medwatch/index.cfm?action=reporting.home>).

#### **9.4.4 Events of Special Interest (if applicable)**

Suspected child abuse reporting is mandatory because the study participants include minors; any incidents will be reported to an EHS supervisor. California law stipulates that a provider seeing a child as a patient is not required to report domestic violence or abuse of the parent/caregiver. But the parent/caregiver may choose to make his/her own report by contacting police. We do not anticipate any other events of special interest during the short duration of this study.

### **9.5 Halting Rules**

The frequency of AEs meeting criteria defined in Section 9.3.1 is expected to be very small. If the number of SAEs is large, or of a particular type, NIDCR may temporarily suspend enrollment until a safety review is convened. The objective of such a review

would be to decide whether the study should continue per protocol, proceed with caution, be further investigated, be modified and then continued, or be discontinued.

## **10 STUDY OVERSIGHT**

The principal investigators will be responsible for study oversight, including monitoring safety, ensuring that the study is conducted according to the protocol and ensuring data integrity. The PIs will review the data for safety concerns and data trends at regular intervals, and will promptly report to the IRB and NIDCR any Unanticipated Problem (UP), protocol deviation, or any other significant event that arises during the conduct of the study.

## **11 CLINICAL SITE MONITORING**

The principal investigators and the study team will conduct quality management activities as described in Section 14. There will be no external clinical site monitoring for this developmental pilot study. The PIs will provide monitoring in accordance with the IRB policies. The NIDCR reserves the right to conduct independent audits as necessary.

## 12 STATISTICAL CONSIDERATIONS

### 12.1 Study Hypotheses

Overall, we hypothesize that one reward strategy informed by behavioral economic theory will be more promising for promoting preventive dental care behaviors by parents/caregivers for their children. The pilot trial hypotheses are:

- (a) At least one monetary reward arm (Fixed or Drawing) will have at least 50% of potential participants hypothetically agree to participate and at least 80% of participants willing to accept randomization to an incentive arm (including non-monetary reward control).
- (b) The remaining study objectives are hypothesis-generating and enabling precise sample size calculations for the future Phase II/III trial.

### 12.2 Sample Size Considerations

The pilot trial sample size will not predominantly be driven by statistical power for group comparisons, but rather the sample size to provide estimates and reasonably precise (narrow) confidence intervals (CIs) of effect sizes to be used to plan the future Phase II/III trial. For example, with  $n=12$  per group and  $\alpha=0.05$ , the 95% CI for a proportion is estimated to extend 0.100 to 0.283 from the observed proportion depending on the underlying proportion (ranging from 0.032 to 0.968 with 0.5 having the widest interval). Nevertheless, with 3 groups of 12 and  $\alpha=0.05$ : (1) a one-way analysis of variance is estimated to have 80% power to detect a difference in percent change means of feasibility / acceptability measures when variance of means is 0.024 and a common standard deviation is 0.286 (smaller standard deviations will have greater power); (2) a chi-square test of feasibility / acceptability measures is estimated to have 80% power to detect a difference in proportions characterized when the variance of proportions of 0.066 and an average proportion of 0.547.

### 12.3 Final Analysis Plan

Two types of data analysis will be conducted for the pilot UH2:

(1) Quantitative analysis: To refine sample size, regression analyses (adjusted for *a priori* potential confounders) will be used to estimate differences and confidence intervals among the three arms between baseline 2-month follow-up visits for the percent change in (1) toothbrushing with fluoridated TP, (2) ChildPlus documented dental visits, and (3) both outcomes combined. Percentages and 95% CIs will be estimated for all feasibility (willingness) measures.

(2) Qualitative exploratory analysis: Perceptions of incentives, their conditionality and achievability, and value of proper oral health care for children will be compared by sociodemographic characteristics. We will select the reward arm where at least 50% of potential participants hypothetically agree to participate and in which at least 80% of

participants accept randomization to a reward arm (including the non-monetary reward control). These will be determined at the 2-month follow-up visit with structured and open-ended questionnaires regarding pilot participation.

Among groups declared “acceptable”, “feasible” and “appropriate”, the group with outcomes at least 20% better than the other two groups will be chosen. If no group is at least 20% better, then the one that either 1) has the highest adherence or 2) is declared most “appropriate” (e.g. easier to explain and understand or less resource intensive) will be chosen for the future Phase II/III trial.

Descriptive statistics (means, standard deviations, frequencies, 95% confidence intervals) will be used to summarize the group specific findings. An intention-to-treat (as assigned) approach will be used. Group estimates and percent difference for parents/caregivers brushing children’s teeth, ChildPlus documented dental attendance, EHS staff participation, parent/caregiver participation (informed consent), willingness to be randomized, willingness to sync smart TB to app, acceptability of the smart powered TB, child willingness to cooperate with dental screening, extraoral photo and plaque assessment, willingness to bring the TP pump to the 2-month visit, item completion/missingness among the 3 groups will be estimated with standard errors and 95% confidence intervals (CIs) to provide valid and precise estimates for sample size calculations for the future Phase II/III trial. If data are not Normally distributed, Normalizing transformations or nonparametric methods will be used. Multiple imputation models will be used for missing data. Although this pilot is not primarily focused on testing for statistically significant differences among groups, analysis of covariance (or nonparametric analysis of covariance) adjusting for potential confounders will be used to estimate effect sizes of the two monetary reward groups versus the control non-monetary reward condition to be used in sample size calculations.

Toothbrushing measures (smart powered TB, parent/caregiver diaries), child plaque scores, TP usage (change in pump weight) will be compared with Pearson (or nonparametric Spearman) correlation coefficients to assess consistency in the various measures. Toothbrushing measures (smart powered TB, parent/caregiver diaries) will be examined overall and by group over time (2 months) to assess for possible temporal effects (e.g., short-term smart powered TB novelty effect). Validity of the TB measures will be assessed by evaluating concordance of: TB diaries with smartphone app TB data; TB diaries with DI plaque score; TB diaries with TP pump weight change; smartphone app TB data with DI plaque score; smartphone app TB data with TP pump weight change; and DI plaque score with TP pump weight change.

---

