#### 3.2 Study Outcome Measures

##### 3.2.1 *Primary*

Acceptability and feasibility of the fixed payment and drawing payment interventions will be measured with the following outcome measures: a) the percentage of half-days (i.e., mornings, evenings) during the study observation period that a parent/caregiver brushes his/her child’s teeth and b) in the subset of children at baseline with no dental visit in the EHS ChildPlus health module, whether or not the child has a ChildPlus documented

dental visit at the three-month follow-up. The feasible and acceptable intervention that yields better toothbrushing adherence and dental attendance outcomes will be selected for inclusion in the future trial.

Additional primary outcome measures of the trial intervention include participant acceptability and feasibility measures in the EHS organization, and amongst EHS staff, parent/caregivers and children. Measures include willingness of the following:

- LA County EHS to sign memoranda of understanding;
- EHS staff participation in assisting with recruitment;
- parents/caregivers to provide informed consent and approve access to ChildPlus dental visit data;
- parents/caregivers to be randomized to a study arm;
- parents/caregivers to adhere to study procedures, including completing questionnaire instruments and toothbrushing frequency diaries, bringing toothpaste pump to 2mo follow-up visit; and
- child cooperation with study procedures, including dental screening, extraoral photo and plaque assessment.

Additional acceptability and feasibility measures of the trial intervention will include meeting inclusion criteria (smartphone ownership and SMS texting), willingness to use the products provided, including the TP pump and child and parent comfort level with using the smart, powered toothbrush and privacy concerns related to tracking their toothbrushing habits.

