**c. Pilot evaluation.** As a general overview of activities: each participant will attend two in-person visits (baseline, 2 months) at one of three EHS sites. Each in-person visit will take approximately 2 hours. Bilingual-bicultural staff will conduct computer assisted personal interviews (CAPI) to administer fully structured, objective questionnaires and enter information directly into the secure, web-based data management system, Qualtrics. Dental examination screening data will be entered directly into REDCap in an eCRF adapted from the ASTDD Basic Screening Survey. The smart powered TB and TP pump will be provided at the baseline visit, and study staff will instruct parents/caregivers on their use. Staff will also provide fluoride TP tubes to families to reduce the possibility of other family members using the TP pump. Participants will be asked to bring the TP pump with them to the 2-month follow-up visit; staff will weigh the pump to ascertain this toothbrushing adherence measure. Depending on the information gathered from the qualitative phase of this UH2 study, parents/caregivers will be instructed to regularly (e.g.,

twice a week) download (sync) data from the smart powered TB to their phone app which then is uploaded to the manufacturer's web-based database (cloud) regarding the length of time the TB was used on the child.

Subject participation for this pilot study will take approximately 2-3 months to complete.

If more than one child in the household is eligible to participate in the study, the oldest eligible child will be the index child. The parent/caregiver will be instructed to have each study-eligible child use his/her own smart TB for the duration of the study, but only the index child's TB will be synced to the smart phone app. Each child participant's TB will have a label with his/her name put on the handle along with customized individual stickers to avoid confusion. Participants will be asked not to allow other people to use the study child's smart TB for the duration of the study.

---

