## **5.5 Treatment Assignment Procedures**

Based on multiple discussions with EHS staff, a trial with different programs will need to demonstrate fairness in a transparent way to the parents/caregivers. Thus, during the explanation of the study to the participant, randomization and the rewards program will be explained with a teachback method. Stratified permuted block randomization will be used to assign participating dyads to a study arm, stratifying on EHS site and varying block size to reduce probability of guessing the next assignment. Once eligibility is confirmed and informed consent is documented, the project coordinator will open a sealed opaque envelope with the participant's study ID number to reveal group assignment for the parent/caregiver-child dyad.

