## **6.2 Administration of Behavioral Intervention**

All participants will be instructed to sync their smart powered TB data to the app twice per week. Failure to do so will disqualify the participant from receiving any incentives that week for those in an incentive group. All participants, regardless of group assignment, will receive a fixed payment of \$3 per week for syncing their data every three days (Mondays, Wednesdays, and Fridays specifically). A text message reminder to sync the app will be sent to participants up to every 3 days. For those assigned to the Drawing incentive group, the reminder will also prompt participants to select a drawing number for the coming week. The drawing for performance-based incentives will take place about 72 hours after week's end.

First, all participants will enter a "practice" week at the start of the intervention, during which participants will sync their TB data (and be eligible for the \$3 incentive for syncing), but not be eligible for the performance-based toothbrushing incentive. Following the practice week, participants are eligible to earn incentives over 8 one-week periods for a total of 56 days.

All participants will be notified by text message of their toothbrushing adherence status per the smart powered TB data every week. For participants assigned to a Fixed or Drawing incentive group, the text message will include the amount earned and the total balance accrued thus far during the 2-month pilot trial (i.e., gift cards, virtual drawing tickets and winnings, depending on parental/caregiver reward preferences obtained in the UH2 formative research). Participants will have the option to additionally have the text messages sent to other family members who regularly brush the child's teeth. Contact information for all family members will be obtained at the baseline visit and will initially require that the recipient opt-in: an introductory text message will be sent to the family members asking if they agree to receive the text messages and only those responding in the affirmative will receive text messages during the intervention.

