### **8.4 Toothbrushing Performance and Frequency**

#### **8.4.1 *Toothbrushing Diaries***

Parents/caregivers will be given calendar diaries to track toothbrushing events that can be compared to the smart powered TB's data. The calendar will be explained at baseline by research staff and collected at follow-up.

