## **8.5 Dental Visit Attendance**

Preventive dental visit attendance of participating children will be ascertained through dental exam data from Head Start's ChildPlus Management Software health module. In the subset of children at baseline without any dental visit in the Early Head Start ChildPlus health module, whether or not the child has a ChildPlus documented dental visit at the two-month follow-up will be assessed.

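### Section 12.3 analyses percent change from baseline to 2 months, which does not fit the dental and brushing outcomes defined in Sections 3.2.1 and 8.5

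*Protocol*

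**What the plan says.** Section 12.3 of the protocol, under quantitative analysis, uses adjusted regression to "estimate differences and confidence intervals among the three arms between baseline 2-month follow-up visits for the percent change in" three things: brushing with fluoridated toothpaste, ChildPlus-documented dental visits, and both together. The stated purpose is to refine the sample size of the later trial. The section does not say whether the change is relative or in percentage points, what the baseline value of each outcome is, or how the two outcomes are combined.

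The outcomes are defined elsewhere:

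- **Brushing** (Section 3.2.1) is "the percentage of half-days (i.e., mornings, evenings) during the study observation period" in which the caregiver brushes the child's teeth.
- **Dental visit** (Section 3.2.1) is yes or no at follow-up, "in the subset of children at baseline with no dental visit in the EHS ChildPlus health module". Section 8.5 repeats the restriction: "In the subset of children at baseline without any dental visit in the Early Head Start ChildPlus health module".

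On when measurement starts, Section 4 says "The smart powered TB and TP pump will be provided at the baseline visit", and Section 8.4.1 says of the diary "The calendar will be explained at baseline by research staff and collected at follow-up". Section 8.2 adds that current brushing is asked by questionnaire at baseline and at 2 months.

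Later in Section 12.3 the protocol also plans group estimates and percent differences among the three groups with 95% confidence intervals, and ANCOVA effect sizes for each incentive arm against control.

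**The concern.** The outcome definitions describe levels observed after randomisation. The regression target describes a change from a starting value. For the dental outcome the starting value is fixed at zero by the definition of the subset. For the half-day brushing outcome it was never measured. The analyst would have to choose the scale, the baseline and the population for each regression, and the protocol does not settle any of these.

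At stake are the effect sizes and intervals carried into the sample size of the Phase II/III trial. With 12 dyads per arm those estimates are imprecise already, so a choice of scale or population made after seeing the data could move them noticeably.

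**Working it through.** **The plan's own figures.** Section 12.2 gives 12 per arm, variance of means 0.024 and SD 0.286 for an ANOVA on percent change means, and variance of proportions 0.066 with average proportion 0.547 for a chi-square test. Both are stated to have 80% power at alpha 0.05.

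- ANOVA: noncentrality 36 × 0.024 / 0.286² = 10.56; noncentral F with 2 and 33 df gives power 79.99%.
- Chi-square: noncentrality 36 × 0.066 / (0.547 × 0.453) = 9.59; 2 df gives power 79.8%.
- Interval half-width for a proportion, 1.96 × √(p(1−p)/12): 0.0996 at p = 0.032 or 0.968, and 0.2829 at p = 0.5. The stated range is 0.100 to 0.283.

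These all reproduce, so the point does not concern the arithmetic of Section 12.2. That section speaks of percent change without giving the scale either. An SD of 0.286 fits a 0-to-1 or percentage-point scale better than an unbounded relative change, but that is an inference.

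**Dental visit in the defined subset.** The baseline is 0 for every child. With follow-up proportion p:

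- relative change = (p − 0)/0, undefined for every p;
- percentage-point change = p − 0 = p, the follow-up proportion itself.

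**Dental visit over all dyads.** Section 12.3 does not repeat the subset restriction, so this reading is possible, although it departs from Sections 3.2.1 and 8.5. Let b be the share already documented at baseline and q the uptake in the rest. The change is (1 − b)q in points and (1 − b)q/b relative. The protocol does not give b, so the range is assumed, with q = 0.5 throughout:

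| b | Points, all dyads | Relative, all dyads | Points, subset |
|---|---|---|---|
| 0.25 | 37.5 | 150% | 50 |
| 0.50 | 25.0 | 50% | 50 |
| 0.75 | 12.5 | 16.7% | 50 |

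The same uptake gives very different figures, because a child already documented cannot improve.

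**Brushing.** The smart toothbrush and the diary both start on Day 0, so no home half-days precede randomisation at that visit. Appendix A marks toothbrushing reports at Day 0, but neither source can supply earlier home data. Two substitutes might be proposed:

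- Questionnaire self-report is a different instrument from the half-day measure.
- The practice week in Section 6.2, in which participants sync data "but not be eligible for the performance-based toothbrushing incentive", falls after randomisation and after the arm has been explained (Section 7.2). It is not a clean baseline.

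Scale matters here as well. Taking 14 brushings a week as 100%, a caregiver who reaches 14 from an assumed start shows:

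| Start per week | Relative change | Points |
|---|---|---|
| 0 | undefined | +100 |
| 1 | +1300% | +93 |
| 7 | +100% | +50 |
| 10 | +40% | +29 |

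**Combined outcome.** One component is binary and exists only for the no-visit subset; the other is a percentage for all dyads. No rule joins them.

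**What the follow-up comparison can deliver.** The subset size is not given. Assuming 4, 6, 8 or 12 children per arm and p = 0.5, the approximate 95% half-width of an arm difference, 1.96 × √(2p(1−p)/m), is 0.69, 0.57, 0.49 or 0.40. The comparison can be estimated but is imprecise.

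**The case against.** The strongest reply is that Section 12.3 does not depend on percent change. It also plans group estimates, percent differences between groups and ANCOVA effect sizes, none of which needs a baseline value. A reader might infer that neither behaviour can be analysed as written; these passages show otherwise. A reader might also infer that the choice of arm rests on percent change. The selection rule in Section 12.3 instead asks whether one group's outcomes are at least 20% better than the others', and falls back on adherence or appropriateness.

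The defence can add that percent change may mean percentage points, in which case the dental quantity is computable; that baseline self-report does exist and could be compared with self-report at 2 months; and that a statistical analysis plan, not shown here, may settle the details. It is also tempting to argue that subtracting self-report from device data would widen the intervals, or that counting the practice week would dilute the arm difference. No passage plans that subtraction. Section 6.2 separates the practice week from the 8 incentive weeks, and a dilution would require assuming no arm difference in that week.

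All of this stands. It does not remove the mismatch. The between-group analyses are not said to replace the percent-change regressions, the ANCOVA names no outcome variable, and the percentage-point reading rescues the dental outcome only by making the baseline term empty. A change in self-report is not the half-day outcome of Section 3.2.1. The conflict lies between stated sections of the protocol, not in detail left for later.

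**Conclusion.** The point holds as an internal conflict. The regression target in Section 12.3 does not match the outcomes in Sections 3.2.1 and 8.5. In the defined dental subset, relative change is undefined for every child and percentage-point change equals the follow-up proportion. The half-day brushing measure has no value before randomisation. The combined outcome has no definition.

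The statement that relative change is undefined rests on the relative reading and on the subset restriction; over all dyads the baseline need not be zero. The size cannot be given as a single bias, because the protocol fixes neither scale, baseline nor population. The tables above show the spread under assumed values. A workable between-group analysis already stands in the same section, so the trial's behavioural data are not lost. What is needed is a clear statement of which quantity is estimated, made before analysis.

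**What to change.** In Section 12.3, replace percent change with between-arm differences in follow-up values:

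- **Brushing:** percentage of half-days brushed over a stated window, for example the 8 incentive weeks (56 days × 2 = 112 half-days), by ANCOVA adjusting for baseline self-reported brushing frequency and EHS site. Site is the randomisation stratum (Section 5.5: "stratifying on EHS site and varying block size to reduce probability of guessing the next assignment").
- **Dental visit:** in children without a documented visit at baseline, the risk difference in documented visits at follow-up, with a small-sample confidence interval.
- **Combined outcome:** drop the percent change, or define it as a follow-up measure and state its population.

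State that these are the estimates to be carried into the Phase II/III sample size. Section 3.2.1 places the dental outcome at three months, while Sections 4, 6.2, 8.5 and 12.3 refer to 2 months; these passages must be reconciled.

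The cost is wording only, since every variable is already collected. With three sites, adjustment uses about 2 degrees of freedom for site and 1 for baseline self-report, leaving 33 − 3 = 30 residual degrees of freedom if all 36 dyads contribute.

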### 3 OBJECTIVES

#### 3.1 Study Objectives

This Phase I pilot trial will test two intervention regimens versus a control regimen to determine which intervention will be used for the future Phase II/III trial and will finalize the outcome measures to be used in the future trial.

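### The arm-selection rule in Section 12.3 admits the control as a candidate, gives its 20% margin no scale or single outcome, and leaves the fallback criteria unordered

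*Protocol*

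**What the plan says.** The protocol states the purpose of the selection twice and the rule twice.

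- **Purpose.** Section 3.1 says the pilot will "test two intervention regimens versus a control regimen to determine which intervention will be used for the future Phase II/III trial". The Protocol Summary says the same.
- **Rule, Section 3.2.1.** "The feasible and acceptable intervention that yields better toothbrushing adherence and dental attendance outcomes will be selected" for the future trial. There is no margin, no fallback and no appropriateness criterion beyond being feasible and acceptable.
- **Rule, Section 12.3.** Arms first pass a willingness gate: at least 50% of potential participants hypothetically agree to take part, and at least 80% of "participants accept randomization to a reward arm (including the non-monetary reward control"). Among the arms that pass, "the group with outcomes at least 20% better than the other two groups will be chosen". Failing that, "If no group is at least 20% better, then the one that either 1) has the highest adherence or 2) is declared most" appropriate, for example easier to explain or less resource intensive.
- **Outcomes in play.** The regression analyses in Section 12.3 cover three: "1) toothbrushing with fluoridated TP, (2) ChildPlus documented dental visits, and (3) both outcomes combined". The selection sentence says only outcomes, in the plural.

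**The concern.** Choosing the arm to carry forward is a stated purpose of this pilot, so the rule should give one answer for a given set of results. As worded it may not, for four reasons.

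1. It ranks groups and asks the winner to beat both others. That makes the control a formal candidate, against the stated purpose.
2. A 20% advantage can mean 20 percentage points or a ratio of 1.2. At an adherence of 50% these are leads of 20 points and 10 points.
3. Brushing and dental visits can favour different arms, and the rule does not say which counts or how they combine.
4. The two fallback criteria have no order. When they point to different arms, whoever applies the rule picks the criterion, and can do so knowing the results.

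At stake is freedom from bias in the choice of intervention for the Phase II/III trial.

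**Working it through.** **Step 1: set the sections side by side.**

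| Element | Sections 3.1 and 3.2.1 | Section 12.3 |
|---|---|---|
| Candidates | the two interventions | all three groups, each against the other two |
| Outcome | brushing and dental attendance | outcomes, not named |
| Margin | none | 20%, no scale |
| If margin missed | not applicable | highest adherence or most appropriate, no order |

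These differences stand on the text and need no calculation.

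**Step 2: reproduce the protocol's own figures (Section 12.2, 12 per arm, alpha 0.05).**

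- CI half-width 1.96·√(p(1−p)/12): 0.100 at p = 0.032 and 0.283 at p = 0.5. Both match.
- ANOVA: noncentrality 36 × 0.024 / 0.286² = 10.56 with 2 and 33 df gives power 0.80. Matches.
- Chi-square: noncentrality 36 × 0.066 / (0.547 × 0.453) = 9.59 with 2 df gives power 0.80. Matches.

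The sample-size arithmetic is sound. The protocol gives no operating characteristics for the selection rule.

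**Step 3: how often would the margin be missed?** Inputs from the protocol: 12 per arm and SD 0.286. The true arm means are assumptions, because none is stated. Applying 0.286 to brushing adherence is also an assumption, because Section 12.2 gives it for percent change in feasibility and acceptability measures.

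SE of an arm mean = 0.286/√12 = 0.0826. SE of a two-arm difference = 0.286·√(2/12) = 0.117, so the 95% half-width is 2.03 × 0.117 = 0.24, wider than a 0.20 margin.

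Arm means were simulated as normal, on brushing alone. The margin is met if the top arm is at least 0.20 above the second (points) or at least 1.2 times the second (relative).

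| True means, control / incentive / incentive | Missed, points | Missed, relative |
|---|---|---|
| 0.5 / 0.5 / 0.5 | 97% | 73% |
| 0.4 / 0.5 / 0.5 | 95% | 65% |
| 0.5 / 0.6 / 0.6 | 95% | 73% |
| 0.4 / 0.6 / 0.6 | 92% | 66% |
| 0.4 / 0.5 / 0.6 | 84% | 51% |
| 0.4 / 0.4 / 0.6 | 67% | 28% |
| 0.4 / 0.4 / 0.7 | 31% | 8% |

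At the variance of means used in Section 12.2 (0.024), a single leader is √(0.024 × 9/2) = 0.329 ahead. The margin is then missed in 22% (points) or 4% to 7% (relative, control mean 0.3 to 0.5).

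**Step 4: do scale and outcome matter?** Across ten patterns of means with SD 0.286 or 0.20, the two scales disagree on whether the margin is met in 8% to 51% of simulated trials. With brushing means 0.4/0.5/0.6, visit rates 0.3/0.4/0.5 and independent outcomes, the top arm differs between brushing and visits in 45%. Visits count only in children with no baseline ChildPlus visit, so that comparison may rest on fewer than 12 per arm.

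**Step 5: the control.** With all means at 0.5, the control has the highest mean in 33% of trials but clears the margin in only 1% (points) or 9% (relative). With means 0.4/0.5/0.5 it ranks highest in 8.5%.

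**The case against.** The best defence is context. This is a 36-dyad pilot whose sample size is not driven by group comparisons, and some discretion over cost and ease of explanation is legitimate. Sections 3.1 and 3.2.1 speak of interventions, and Section 12.1 describes a monetary reward arm as Fixed or Drawing, so the word group in Section 12.3 may be loose drafting. It is also sensible that an incentive far above control should miss a margin meant to separate two incentives when the other is close behind. All of this is fair. It limits the severity but does not settle which sentence governs. The rule is fixed in the protocol itself, so it is not detail left to a statistical analysis plan.

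A reader might infer three stronger points that the document does not support.

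- **That the fallback usually decides.** This depends on means the protocol does not give and on a borrowed SD. With one arm 20 points ahead, the relative margin is missed in only 28% of trials.
- **That the control would be chosen a third of the time if nothing works.** Ranking first is not being chosen. The control clears the margin in 1% to 9%, and in the fallback highest adherence is only one of two criteria. If the incentives work, its selection is unlikely.
- **That the rule can never conclude that neither incentive beats control.** A win for the control would say so in effect, and the willingness gate could leave no candidate. What is missing is an explicit statement of that result.

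**Conclusion.** Wrong as written. Section 12.3 conflicts with Sections 3.1 and 3.2.1 on who the candidates are, and with Section 3.2.1 on margin and criteria. Its margin cannot be applied without first choosing a scale and an outcome, and its fallback can be resolved after the data are seen.

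The practical weight lies where the two incentives perform similarly. With both 10 points above a control of 40% or 50%, the margin is missed in about 65% to 73% of trials on the relative scale and 95% in percentage points, given SD 0.286, 12 per arm and brushing alone. An arm that leads by 20% on every outcome and on both scales would be picked by the data, and the point does not touch that case.

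**What to change.** Before any outcome data are seen, amend Section 12.3 to:

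1. limit the candidates to Fixed and Drawing, use the control only as a benchmark, and allow a result of no arm selected if neither exceeds it;
2. name the outcome to which the 20% applies, or state how brushing and dental visits are combined;
3. say whether 20% is relative or in percentage points;
4. put highest adherence and most appropriate in a fixed order;
5. agree with Section 3.2.1, so that one rule stands in both places.

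The scale, the order and the role of dental visits are for the sponsor to choose. One consequence should be known first. A 20-point margin between Fixed and Drawing would be missed about 91% of the time if they do not truly differ (0.20/0.117 = 1.71 standard errors), so on that scale the first-ranked fallback criterion would often make the choice.

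The cost is wording only. The downside is less discretion once the results are in.
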